### Sample size calculation and statistical considerations

At present, in the ICU antibiotic therapy is employed in 40% of patients, which represents a decline from our original survey conducted in 1998 (up to 80% of all patients) [3]. The expected reduction in antibiotic usage is 10–25%, with a clinically relevant reduction considered to be any reduction in excess of 10%. The minimum number of days of hospitalization in each arm required to detect a 10% reduction with a type I error under 5% and a power of 80% is 2300. The expected follow up rate is in excess of 90%. Because the unit of randomization is days and not individuals, an unknown intracluster (intraday) correlation coefficient must be considered. The standard χ^2 ^statistic, which assumes independence of individuals, may not be applicable. We may be forced to acknowledge the nested nature of the data (clustered randomized controlled trial) by using test statistics based on the generalized linear mixed model [12]. To safeguard against insufficient power we believe that the sample size must be increased to 25%, leading to a required accrual of 3000 hospitalization days per arm. Given the size of the participating units, this translates to a study duration of 24 months.

All analyses will be carried out on an intention-to-treat basis. This means that any antibiotic treatment course will be allocated according to the randomization status of the day on which the decision to withhold or to continue had to be made. This requires us to perform three subgroup analyses: antibiotic prescription prevalence according to the day's randomization status; antibiotic free days following the 4 days after any microbiological work up; and antibiotic free days during the week following any initiation of antibiotics.

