### Setting

The participating university hospital is the tertiary referral centre for Eastern and Southern Switzerland, and serves a population of approximately 3 million. The Department of Neonatology and Pediatric Intensive Care at the University Children's Hospital of Zurich contributes patients from its two ICUs, named unit A and unit B. Both units have average occupancy of 8–10 beds. The two units admit between 900 and 1000 patients annually, with the number of hospitalization days amounting to 5500 each year. The patient population in unit A includes infants of extremely low birth weight referred from other hospitals, critically ill children and adolescent patients, trauma victims and high-risk surgical patients. Unit B predominantly cares for infants and children who have undergone cardiac surgery.

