### Randomization

The units of randomization are calendar days. Randomization is generated through pre-specified assignment of 15 working days/month as intervention days. Physicians remain blinded to the allocation roster. Thirty minutes after the deadline for delivery of samples to the laboratory (10 a.m.), physicians are informed about the randomization status (control or intervention) of the day. In this way, physicians are able to adjust their decision making while they await test results if they so wish.

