### Data collection

Routine sepsis work up includes collection of blood cultures, other microbial specimens where appropriate, and measurements of white blood cell count, including differential and plasma levels of C-reactive protein. Routine surveillance for ventilator-associated pneumonia comprises microbiological examination of the tracheal aspirate, including cultures. As described above, physicians must provide two probability estimates, one for the presence of sepsis and one for pneumonia, whenever they order a sepsis or pneumonia work up. This ensures that clinicians state their estimate before knowledge of the test result. These estimates (pre-test probabilities) are integrated with cytokine concentrations derived from likelihood ratios for sepsis or pneumonia using Bayes' theorem. The algorithms for calculating post-test probabilities are presented in Table 1. A study nurse records clinical data for both groups on the day preceding collection of culture specimens and on the following 6 days (Fig. 3). We will collect data on mortality, but this will not be included as a study outcome because of low mortality rates and the intended study size. Further data are collected from the hospital's database. This database contains all physician's reports, patient baseline data, routine laboratory results, pharmacology data, costs per patient and day of specific medications (e.g. fresh frozen plasma), and staff allocation.

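### The tests named for the primary antibiotic-use rate carry no term for month block or unit, though both are known for every hospitalization day; adding them is a free but modest improvement

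*Protocol article*

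**What the plan says.** The primary outcome is systemic antibiotic use per 1000 days of hospitalization (Measures of outcome), which refers the reader to the sample size section for details. That section mentions the standard chi-square statistic, says it may not apply because days rather than individuals are randomized, and allows for "using test statistics based on the generalized linear mixed model" if the clustering has to be acknowledged. It neither lists nor excludes terms other than arm. Adjustment for patient confounders appears only in the description of the secondary outcomes.

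Two features of the design bear on this:

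- Allocation is set within months: "Randomization is generated through pre-specified assignment of 15 working days/month as intervention days" (Randomization).
- The units treat different patients. Unit A takes extremely low birth weight infants, critically ill older children, trauma and high-risk surgery, whereas "Unit B predominantly cares for infants and children who have undergone cardiac surgery" (Setting).

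Other information exists only around work-ups. Two pre-test probabilities are mandatory in both arms when a work-up is ordered: "This ensures that clinicians state their estimate before knowledge of the test result" (Data collection). The day's status is announced 30 minutes after the 10 a.m. sample deadline (Randomization). Clinical data are tied to cultures: "A study nurse records clinical data for both groups on the day preceding collection of culture specimens and on the following 6 days" (Data collection).

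**The concern.** Month is the block within which allocation is fixed, so the analysis should reflect it. Antibiotic use in this setting moves over time: the article reports a fall from up to 80% of patients in 1998 to 40%, and the trial runs for 24 months. The quota is a fixed count of days, so the share of intervention days varies with the length of the month. If controls are the remaining working days (the article does not say) and months have 20 to 23 of these, the share runs from 15/23 = 65% to 15/20 = 75%. A comparison pooled over months then lets some drift into the arm contrast, and leaves between-month variation in the error.

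Unit is expected to be balanced, since a calendar day's status applies to both units. Balance guards against bias, but it does not remove the variance due to two different case mixes. Power is a worry that the article itself raises, and both variables are already at hand.

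**Working it through.** **1. Reproduce the plan's figure.** Inputs, all from the sample size section: baseline "At present, in the ICU antibiotic therapy is employed in 40% of patients", read as a proportion of days, p1 = 0.40; "The minimum number of days of hospitalization in each arm required to detect a 10% reduction", read as relative, p2 = 0.36; "with a type I error under 5% and a power of 80% is 2300". Two-sided testing is assumed.

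n per arm = [z(0.975)·√(2·p̄·(1 − p̄)) + z(0.80)·√(p1(1 − p1) + p2(1 − p2))]² / (p1 − p2)², with p̄ = 0.38

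= [1.960 × 0.6864 + 0.8416 × 0.6859]² / 0.0016 = 2311 (rounded up).

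This agrees with 2300. A one-sided test gives 1820 and does not. The sizing is therefore that of a crude comparison and takes no credit for block or covariates.

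**2. Power before adjustment.** Accrual is 3000 days per arm. Taking the stated 25% increase as a design effect of 1.25 (assumption) gives 3000 / 1.25 = 2400 effective days. The final level is 0.04 (Stopping rules).

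Power = Φ{[0.04·√2400 − z(0.98)·0.6864] / 0.6859} = 0.789.

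**3. What unit alone might explain.** With two equal-sized units around a mean of 0.38 (assumption), R² = (d/2)² / (0.38 × 0.62), where d is the difference in antibiotic use between units:

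- d = 10 points: 0.05² / 0.2356 = 0.011
- d = 20 points: 0.10² / 0.2356 = 0.042

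The documents give neither d nor any R². A range of 0.01 to 0.05 for month and unit together on the all-days rate is an assumption guided by these values.

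**4. Power after adjustment.** Effective days become 2400 / (1 − R²):

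| R² (assumed) | Effective days per arm | Power at 0.04 |
|---|---|---|
| 0 | 2400 | 0.789 |
| 0.01 | 2424 | 0.793 |
| 0.03 | 2474 | 0.801 |
| 0.05 | 2526 | 0.809 |

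The (1 − R²) rule belongs to linear models. For a binary daily outcome in a logistic mixed model it is only approximate, and the adjusted odds ratio is also a different quantity from the marginal one.

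**5. Which variables can be used where.**

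| Variable | Available for | Use |
|---|---|---|
| Month, unit | every hospitalization day | all analyses |
| Two pre-test probabilities | days with a work-up or antibiotic prescription | analyses based on work-ups |
| Nurse-recorded prior-day data | around cultures only | not for the all-days rate |

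Prior-day antibiotic status has a further difficulty. Days are randomized, so a patient's status yesterday may already reflect the allocation of earlier days.

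**The case against.** The strongest objection is that the article never says the primary analysis is unadjusted. A reader might infer that from its silence, but a mixed model can carry fixed effects, neither candidate test is firmly chosen, and a covariate list is commonly left to the full protocol or analysis plan. This stands: the silence is not an error. What remains is that month is part of the allocation scheme, and that adjustment is mentioned for the secondary outcomes but not for the primary one. Naming month and unit improves on the tests as stated.

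A reader might also infer a large loss of power, on the view that pre-test probability strongly predicts treatment. If R² were 0.10 to 0.30, power would rise to 0.831 to 0.913. The documents do not support this for the primary rate. Its denominator is all hospitalization days, and pre-test estimates exist only where a work-up or prescription occurred. If 10% to 30% of days had an estimate, with R² of 0.30 within them (both assumed), the overall R² would be 0.03 to 0.09, and even that could not be obtained by direct adjustment of the all-days model.

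Finally, a month term might be thought to answer the control-arm learning that the Discussion foresees. It does not: learning shrinks the difference between arms within each month, and no calendar term restores it. The monthly quota also already limits bias from drift by spreading intervention days over the calendar.

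**Conclusion.** The point holds as a free improvement, not as an error in the plan. The tests named for the primary rate have no stated term for the block in which days are allocated or for a unit split with different case mix, although both are known for every day. On the assumptions shown (40% against 36%, 3000 days per arm, design effect 1.25, final level 0.04, R² of 0.01 to 0.05), power goes from about 79% to between 79% and 81%. Under the same assumptions, an R² of about 0.03 would bring it back to 80%. Larger gains are possible only in the work-up-based analyses. The month term removes between-month drift from the comparison and leaves control-arm contamination untouched.

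**What to change.** State one primary analysis in advance: a mixed model that respects clustering by day, with fixed effects for arm, month block and unit.

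In the analyses of antibiotic-free days after a work-up or after initiation, add the two pre-test probabilities, restricted to estimates written before the day's status was disclosed; the article does not say how work-ups ordered later in the day are handled. Leave out prior-day antibiotic status, or use it only with a stated estimand that allows for the effect of earlier days' allocation.

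The cost is wording in the analysis section. No new data and no additional hospitalization days are needed.

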### Stopping rules

Twelve months after initiating the trial, we will conduct an interim analysis at a two-sided *P *< 0.01 level. If the results indicate no trend toward a change (increase or reduction) in antibiotic treatment (curtailment from 48 to 24 hours) in prophylactic empirical therapy, and if there is no trend at the *P *< 0.1 level toward improved secondary outcomes, then the trial will be discontinued. The interim analysis implies that the result of the final analysis should be considered significant if *P *< 0.04.

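### The 3000 days per arm, the 24-month duration and the stated 5500 days a year do not reconcile, and the size is computed at 0.05 although the final test is at 0.04

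*Protocol article*

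**What the plan says.** The Setting section describes two intensive care units, "with the number of hospitalization days amounting to 5500 each year". The sample size section starts from the statement that "in the ICU antibiotic therapy is employed in 40% of patients" and gives the minimum number of days per arm "required to detect a 10% reduction with a type I error under 5% and a power of 80% is 2300". It then says "The expected follow up rate is in excess of 90" per cent. It notes that the correlation within a day is unknown, and adds 25% as a safeguard, "leading to a required accrual of 3000 hospitalization days per arm". It concludes that, for units of this size, "this translates to a study duration of 24 months".

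The Stopping rules section says: "Twelve months after initiating the trial, we will conduct an interim analysis". That look uses a two-sided 0.01 level and can end the trial if no trend is seen. The final result is then to be judged at 0.04.

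The Randomization section names the calendar day as the unit, and assigns 15 working days a month to intervention. The Discussion treats the 24 months as required and lists the length as a limitation, because learning may spill over into the control arm.

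**The concern.** Two sets of figures that should follow from one another do not.

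First, the day target and the duration differ by almost a factor of two at the stated annual volume. A reader cannot tell whether the trial ends at 6000 days or at 24 months (about 11,000 days). The choice decides the power, and whether the 12-month look comes half-way or close to the end. It also decides whether the 24 months listed as a limitation is needed at all.

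Second, the base size is computed with "a type I error under 5" per cent, but the final test is stricter. The step to 3000 shows no separate allowance for the stricter level or for follow-up loss.

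**Working it through.** **Inputs.** Control rate 40% (stated per patient, used here as the proportion of days on antibiotics); 10% relative reduction, so 36%; power 80%; sizing level 0.05; final level 0.04; follow-up above 90%; inflation 25%, read as a factor of 1.25; 5500 days a year for both units together.

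**Base size.** With p̄ = 0.38, n per arm = [z(1−α/2)·√(2 × 0.38 × 0.62) + z(0.80)·√(0.40 × 0.60 + 0.36 × 0.64)]² / 0.04².
- At two-sided 0.05: (1.960 × 0.6864 + 0.842 × 0.6859)² / 0.0016 = 2311. The plan's 2300 reproduces. One-sided 0.05 gives 1820 and does not.
- At two-sided 0.04 (z = 2.054): 2468.

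**Inflation.**
- 2300 × 1.25 = 2875. Rounding up to 3000 leaves room for 1 − 2875/3000 = 4.2% loss.
- 2300 × 1.25 / 0.9 = 3194.
- At 0.04: 2468 × 1.25 = 3085 with full follow-up, and 3085 / 0.9 = about 3430 with 90% follow-up.

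**Power.** Effective days per arm = accrued days × follow-up / design effect, put into the same formula:

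| Accrued days per arm | Follow-up | Design effect | Effective days | Power at 0.05 | Power at 0.04 |
|---|---|---|---|---|---|
| 3000 | 90% | 1.25 | 2160 | 77.3% | 74.4% |
| 3000 | 100% | 1.25 | 2400 | 81.5% | 78.9% |
| 3000 | 90% | 1.00 | 2700 | 85.7% | 83.5% |
| 3000 | 100% | 1.00 | 3000 | 89.1% | 87.3% |
| 5500 (24 months) | 90% | 1.25 | 3960 | – | 94.7% |
| 5500 (24 months) | 100% | 1.25 | 4400 | – | 96.5% |

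At 0.04, 3000 per arm holds 80% only up to a design effect of 2700/2468 = 1.09 with 90% follow-up, or 3000/2468 = 1.22 with full follow-up. Both are below the plan's own 1.25.

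**Duration.**
- All days count: 6000/5500 × 12 = 13.1 months. If 6000 must remain after 10% loss, 14.5 months.
- 24 months: 2 × 5500 = 11,000 days, 5500 per arm. For 24 months to be needed for 6000 days, only 6000/11,000 = 55% of the stated days could count.
- Weekdays only, split 1:1 (assumption): 5/7 × 5500 = about 3930 days a year, so 18.3 months, or 20.4 with 10% loss.
- A variant with 252 working days a year at 15 patients (assumption): 3780 days a year, so 19.0 months, or 21.2 with loss.
- Weekdays only with 15 intervention days among an assumed 21 to 22 working days a month: the control arm alone needs about 30 to 33 months to reach 3000.

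**Interim at 12 months.**
- Months govern: 5500/11,000 = 50%.
- Days govern, all days count: 5500/6000 = 92%.
- Days govern, weekdays only: 3930/6000 = 65%, or 3780/6000 = 63% on the 252-day variant.

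**The case against.** The strongest reply is that the two discrepancies offset each other. The protocol calls 3000 a required accrual and nowhere says that recruitment ends there. It gives 24 months twice and places the interim at half of that. If 24 months at the stated volume is what will be run, power is about 95% even at 0.04 with 90% follow-up and a design effect of 1.25. This stands, and it limits the practical harm. It does not reconcile the figures, because the plan derives the 24 months from the 3000.

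A reader might infer that the plan's inputs give 74% power. The document does not support that as a single figure. Follow-up is said to exceed 90%, so 90% is the floor, and the correlation within a day is unknown, so 1.25 is an allowance and not an estimate. The 74% is the low corner of a range that reaches 87% without clustering. Nor is 2875 against 3000 an error in itself: it is rounding in the safe direction.

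A reader might also infer that the true duration is 13 to 15 months and that the interim will hold 92% of the data. Both depend on every hospitalization day counting, and the 92% also on 6000 days being the end point. The randomization wording mixes calendar days and working days, and patients transferred within 24 hours are excluded, so the usable volume is not settled. What is shown is that 24 months cannot be derived, not which duration is right.

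One reading comes near 24 months. If the average occupancy of 8 to 10 beds means both units combined, the volume is 2920 to 3650 days a year, and 6000 days take about 20 to 25 months. But 5500 days a year, in the same section, means about 15 occupied beds a day.

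**Conclusion.** Wrong as written; it should be corrected. The firm part is the conflict between target, volume and duration. At 5500 days a year, 6000 days take about 13 months (14.5 with 10% loss; about 18 to 20 on an unstated weekday-only 1:1 reading), while 24 months supplies about 11,000 days. The protocol gives no explanation that closes the gap. As a result, the 12-month look is anything from half to about 92% of the data.

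The power part is smaller and conditional. Because the final level is 0.04, the plan's own 25% clustering inflation calls for about 3085 days per arm at full follow-up and about 3430 at 90%. At 3000 the power is 74 to 79% if clustering uses the whole allowance, and 83 to 87% if there is none. The shortfall matters only if the trial stops at 3000 per arm. All power figures assume 40% against 36% of days on antibiotics and a two-sided test.

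**What to change.** - State whether accrued days or calendar months end the trial, and which days count: all calendar days or working days only, the allocation ratio that follows, and the effect of excluding early transfers.
- From that one choice, restate the target per arm, the duration and the power. Compute power at 0.04 with follow-up loss, as a range over the design effect and not as one value.
- Give the interim's information fraction on the same basis, so that the 12-month look is the half-way look that it appears to be meant as.
- Correct the Setting figures if 5500 days and 8 to 10 beds describe different things.

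The cost is restated figures in the sample size and stopping-rule sections. If 24 months governs, no extra accrual is needed and the stated power rises. If 3000 per arm governs, the plan must state a lower power than 80% over part of the range, and explain the duration.

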## Methods

### Design

The study is a multicentre randomized controlled trial comparing a new diagnostic treatment strategy for diagnosing bacterial infection versus standard care in critically ill newborns and children. During a 16-week period in 2003 we conducted a pilot study, which tested the intervention and data collection procedures, and led to modifications to the study design. The pilot study is outlined in detail below. In brief, physicians provide pre-test probabilities whenever they order a diagnostic work up for sepsis or ventilator-associated pneumonia (microbiological cultures). This includes any prescription of antibiotics. In the intervention arm, physicians are provided with cytokine results and the updated post-test probability. In the control arm no information is given.

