#### Intervention strategy

If patients are randomized to the intervention arm, then physicians are also obliged to document their best estimate of the probability that the patient has sepsis or pneumonia, again on two logarithmic visual-analogue scales (range 0–100%). This documentation is again mandatory and must be marked on the laboratory form (Fig. 1). In the intervention arm, blood or tracheal aspirate specimens are analyzed and results are returned to the unit before 1 p.m. Physicians receive the raw cytokine values as well as the calculated likelihood ratio and the post-test probability (Fig. 2). This information is provided in addition to routinely available data. Provided that the available post-test probability indicates absence of infection, physicians are encouraged to stop antibiotic treatment. It is suggested that antimicrobial therapy be continued if the post-test probability indicates infection. It is important to note that the protocol provides only 'suggestions', and that the final decision regarding therapy is left to the discretion of the responsible clinician. This is similar to clinical routine, in which diagnostic results may suggest alterations to treatment decisions but they do not dictate treatment.

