### Objectives and hypotheses

Our objectives are to achieve a clinically relevant reduction in overall antibiotic use and to reduce treatment costs caused by delayed diagnosis of nosocomial infection. In this study we will test the hypothesis that routine surveillance by determination of cytokine levels in plasma and tracheal aspirates will allow safe discontinuation of antibiotic therapy within 24 hours if the proposed laboratory prediction model indicates absence of infection. We regard a reduction in antibiotic exposure by 15% to be a clinically relevant effect. The second hypothesis we will test is whether early diagnosis reduces the morbidity and costs associated with hospital acquired infection. Ascertaining relevant indicators of morbidity and costs in all patients with culture proven bloodstream infection will operationalize this.

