### Measures of outcome

The primary outcome measure is the rate of systemic antibiotic use per 1000 days of hospitalization (see details under Sample size calculation and statistical considerations). Secondary outcome measures are as follows (for all episodes of hospital acquired infection with positive blood cultures for the first 7 days following initiation of antibiotics after adjusting for important possible patient confounders): number of days free from mechanical ventilation (an indicator of respiratory failure); number of days free from inotropic support (an indicator of circulatory failure); costs for specific expensive medications (e.g. fresh frozen plasma); and nurse allocation (an indicator of treatment intensity).

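### Each antibiotic course is charged to the day of its own decision, so any excess of restarts after intervention-day stops drops out of the primary contrast

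*Protocol article*

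**What the plan says.** All places are in the protocol article.

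- **Randomization:** "The units of randomization are calendar days", and "Randomization is generated through pre-specified assignment of 15 working days/month as intervention days".
- **Design:** a pre-test estimate is due at every work-up, and "This includes any prescription of antibiotics". A restart therefore brings its own estimate on its own day.
- **Intervention strategy:** when the post-test probability points to no infection, "physicians are encouraged to stop antibiotic treatment".
- **Sample size calculation and statistical considerations:** intention-to-treat is defined so that "any antibiotic treatment course will be allocated according to the randomization status of the day on which the decision to withhold or to continue" fell due. Three analyses follow, labelled subgroup analyses. One goes by the status of the day itself. The other two count antibiotic-free days over 4 days after a work-up and over a week after a start of antibiotics.
- **Objectives and hypotheses:** the claim under test is that the strategy "will allow safe discontinuation of antibiotic therapy within 24 hours if the proposed laboratory prediction model indicates absence of infection", together with a reduction in overall antibiotic use.
- **Data collection:** the nurse record is kept "on the day preceding collection of culture specimens and on the following 6 days".

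**The concern.** A stop on an intervention day saves antibiotic days, and these are credited to the intervention arm. If the patient then needs antibiotics again, the new prescription has a new decision day with its own allocation, which may be control. Under the stated rule the days caused by the stop are then not charged to the arm that stopped.

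This matters because restart days are both a cost in antibiotic use and a direct sign that a stop was wrong. The other outcomes do not reliably bring them back. The secondary outcomes are measured "for all episodes of hospital acquired infection with positive blood cultures for the first 7 days following initiation of antibiotics", so a pneumonia with negative blood cultures lies outside them, and mortality is recorded but is not an outcome. The Discussion foresees only spill-over that makes a difference harder to find. An excess of restarts would work the other way and make a saving look larger than it is.

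**Working it through.** **The plan's own figure.** Read the 40% treated as 400 antibiotic days per 1000 hospital days, and a 10% reduction as 0.40 to 0.36. With two-sided 5% and 80% power:

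n = [1.960·√(2·0.38·0.62) + 0.842·√(0.40·0.60 + 0.36·0.64)]² / 0.04² = 2311 per arm.

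The plan states 2300, so this reading of the base rate and effect reproduces it.

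**Inputs**
- Base rate 400 and direct saving s = 40 per 1000 (the 10% of the sample size section).
- Intervention share of days π. If weekends count as control, π = 15/30.44 = 0.493. If only working days are randomized (30.44 × 5/7 = 21.74 a month), π = 15/21.74 = 0.690.
- Excess restart days e per 1000 intervention-day hospital days. The document gives no figure, so a range is assumed.
- The status of the restart day is assumed independent of that of the index day.

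**Attribution.** Out of N hospital days, πN are intervention days and generate πN·e/1000 excess restart days. A share π of these falls on intervention days and 1 − π on control days. Per 1000 days of each arm:

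- intervention: 400 − s + π·(πe)/π = 400 − s + πe
- control: 400 + (1 − π)·(πe)/(1 − π) = 400 + πe

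The difference is s, whatever e and π are. The true net saving is s − e. The reduction shown is s/(400 + πe); the true one is (s − e)/400.

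| s | e | True net | Shown, π = 0.493 | Shown, π = 0.690 |
|---|---|---|---|---|
| 40 | 0 | 10.0% | 10.0% | 10.0% |
| 40 | 10 | 7.5% | 9.9% | 9.8% |
| 40 | 20 | 5.0% | 9.8% | 9.7% |
| 40 | 40 | 0% | 9.5% | 9.4% |
| 60 | 30 | 7.5% | 14.5% | 14.3% |

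The formula also runs the other way. If early rule-in prevents 20 late-start days per 1000 (e = −20), the true reduction is 60/400 = 15.0%, while 40/(400 − 0.493·20) = 40/390.1 = 10.3% is shown.

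**Check with restarts in both arms.** Assume 60% early stops on intervention days and 10% on control days, courses of 1 day if stopped and 2 if not, 20% of stops wrong, and a 5-day restart.
- Charged to the index day: intervention 1.4 + 0.6·0.2·5 = 2.0 and control 1.9 + 0.1·0.2·5 = 2.0, so there is no saving.
- Charged to the restart's own day: each arm carries (0.493·0.6 + 0.507·0.1)·0.2·5 = 0.35, so 1.75 against 2.25 is shown, a reduction of 22%. A simulation gave 22.3% for this rule and 0.4% for index-day charging.

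**What the window analyses recover.** Let an early stop save 1 day, with excess restart probability q and restart length L, restarting on day 3 (assumed). The true saving per stop is 1 − qL. If windows are grouped by index day and each restart also opens a window in the later day's arm, the saving shown is (1 − q·days captured)/(1 + πq), with π = 0.493. The 7-day window captures 5 days and the 4-day window 2.
- q = 5%, L = 5: true 0.75; 7-day 0.75/1.025 = 0.73; 4-day 0.90/1.025 = 0.88.
- q = 10%, L = 5: true 0.50; 7-day 0.50/1.049 = 0.48; 4-day 0.80/1.049 = 0.76.

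Grouped by index day, the 7-day analysis comes close to the truth for restarts that fall inside it.

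**The case against.** The strongest reply is that the article does not define a course. Treatment resumed after a short gap could count as the same course, and a full protocol or SAP might say so. The rule also names the decision to withhold, so a late start may already belong to the day of withholding. Both points stand as ambiguity. They do not remove the problem: the article states an allocation rule, treats every prescription as a new occasion for an estimate, and has no sentence linking a restart to the earlier stop.

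It can also be said that the two window analyses already address the issue. If grouped by the index day's arm they do so in good part, as the arithmetic shows. But they are labelled subgroup analyses, their grouping is not spelled out, and the article does not say which of the three carries the primary rate. The 7-day window opens at the start of antibiotics, so it misses a late start after withholding. Restart days beyond either window escape.

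A reader might infer three stronger things that the document does not support.
- *That the bias always favours the intervention.* It depends on an excess of restarts and reverses if early rule-in prevents late starts.
- *That half of the restart days is lost.* About half of them (51%) fall on control days if weekends count as control, or 31% if they do not. Because both daily rates rise equally, the whole excess leaves the contrast in either case.
- *That net antibiotic use may rise while a saving is shown.* With q = 15% and L = 7 the simple model gives 1 − 1.05 = −0.05 days per stop, but it gives every control course 2 days. Control treatment ends at 48 hours only if blood cultures stay negative. If infected control courses also last 7 days, the control mean is 0.85·2 + 0.15·7 = 2.75, the intervention mean is 1 + 1.05 = 2.05, and the true saving is 0.70. The sign reversal goes. The attribution gap stays, since 2.75 − 1 = 1.75 is shown, again 1.05 too high.

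**Conclusion.** The point holds in conditional form. As worded, the allocation rule makes the primary contrast show the direct saving rather than the net saving. The error equals the excess of restart or late-start days that intervention-day decisions cause or prevent, and it is zero if there is none. Within the illustrated range it can be as large as the 10% reduction on which the sample size rests.

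The conclusion assumes that a restart counts as a new course, that its day's allocation is independent of the index day, and that the primary rate follows the stated rule. The size cannot be fixed from the document, which gives no restart rate. This calls for a correction of the analysis rule and does not invalidate the design. Without it, a positive primary result could not by itself separate a net saving from treatment that was only deferred, nor support the claim of safe discontinuation.

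**What to change.** In Sample size calculation and statistical considerations:

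1. State that antibiotic days from a course restarted or started late within the recorded window, up to day 6 after the index culture, are charged to the arm of the index decision day. Further work-ups inside that window open no new unit, so each antibiotic day counts once.
2. Apply this in the primary outcome and keep it as the stated rate per 1000 hospital days.
3. Group both antibiotic-free-day analyses by the index day's arm.
4. Report restarts and late starts within the window by index arm, as a safety result.

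Conduct and data collection do not change: the nurse record covers the window and the hospital database holds the drug data. The costs are some extra programming, some dilution when a later work-up in the window falls on a day of the other arm, and restart days beyond the window that remain uncharged.
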